# A post-market, prospective, multi-center, single-arm clinical investigation of Phasix™ mesh for VHWG grade 3 midline incisional hernia repair: a research protocol

**DOI:** 10.1186/s12893-018-0439-7

**Published:** 2018-11-20

**Keywords:** Incisional hernia, Complex hernia, Biosynthetic mesh, Mesh repair, Midline laparotomy, Surgical site occurrence, Complications

## Abstract

**Background:**

Incisional heia is a frequent complication of midline laparotomy. The use of mesh in hernia repair has been reported to lead to fewer recurrences compared to primary repair. However, in Ventral Hernia Working Group (VHWG) Grade 3 hernia patients, whose hernia is potentially contaminated, synthetic mesh is prone to infection. There is a strong preference for resorbable biological mesh in contaminated fields, since it is more able to resist infection, and because it is fully resorbed, the chance of a foreign body reaction is reduced. However, when not crosslinked, biological resorbable mesh products tend to degrade too quickly to facilitate native cellular ingrowth. Phasix™ Mesh is a biosynthetic mesh with both the biocompatibility and resorbability of a biological mesh and the mechanical strength of a synthetic mesh. This multi-center single-arm study aims to collect data on safety and performance of Phasix™ Mesh in Grade 3 hernia patients.

**Methods:**

A total of 85 VHWG Grade 3 hernia patients will be treated with Phasix™ Mesh in 15 sites across Europe. The primary outcome is Surgical Site Occurrence (SSO) including hematoma, seroma, infection, dehiscence and fistula formation (requiring intervention) through 3 months. Secondary outcomes include recurrence, infection and quality of life related outcomes after 24 months. Follow-up visits will be at drain removal (if drains were not placed, then on discharge or staple removal instead) and in the 1st, 3rd, 6th, 12th, 18th and 24th month after surgery.

**Conclusion:**

Based on evidence from this clinical study Depending on the results this clinical study will yield, Phasix™ Mesh may become a preferred treatment option in VHWG Grade 3 patients.

**Trial registration:**

The trial was registered on March 25, 2016 on clinicaltrials.gov: NCT02720042.

## Background

Incisional hernia (IH) is one of the most frequent complications after midline laparotomy, with incidences varying from 10 to 20%, and even higher percentages occur in high-risk groups [1, 2]. IH can lead to a high morbidity and reduces quality of life [3, 4]. Due to the high IH incidence rates, hernia repair surgery is one of the most frequently performed surgical procedures [5]. The aim of hernia surgery is to relieve symptoms, to prevent complications or to resolve acute complications.

There are several options for hernia repair, including primary simple suture repair, synthetic or biologic material placement, repair with relaxing incisions, component separation and use of musculofascial flaps, utilizing both open and laparoscopic approaches [6–8]. Synthetic mesh repair procedures, either open or laparoscopic, lead to fewer recurrences compared to primary repair; recurrences after mesh are 7.7% compared to 23.8% after primary closure [1, 3, 9, 10]. Improved outcomes are believed to be related to reduced tension on the fascial edges and sutures when mesh is used in hernia repair procedures. Despite reducing hernia recurrence rates, the use of synthetic mesh has been associated with complications in approximately 17% of patients. These complications include infection, pain, adhesions, fistulae and foreign body reactions including increased inflammation and/or connective tissue deposition [3, 11]. Especially complex and large abdominal wall defects continue to pose a challenge to surgeons, which are associated with recurrence rates of up to nearly 40% [12].

It can be stated that synthetic mesh is more prone to infection than primary closure, and this poses a problem in potentially contaminated hernias like Ventral Hernia Working Group (VHWG) Grade 3 hernias [13] (Fig. 1). The success of the mesh repair is jeopardized by potential contamination due to complicating factors like previous wound infection, the presence of a stoma or violation of the gastro-intestinal tract.

**Fig. 1 Fig1:**
[figure not shown]
Hernia grading system: assessment of risk for surgical site occurrences [13]. (Reprinted from Surgery, 148(3), The Ventral Hernia Working Group, Incisional ventral hernias: Review of the literature and recommendations regarding the grading and technique of repair, 544-558, Copyright (2010), with permission from Elsevier)

The use of a biological tissue matrix has been advocated in (potentially) contaminated hernias, because of their ability to resist infection, milder inflammatory response and more orderly collagen deposition than non-resorbable, synthetic meshes [14–16]. Most often, biological meshes are derived from human, porcine or bovine dermis, and these materials have been processed to acellular sheets of collagen and elastin. The development of resorbable mesh products has faced challenges related to the rate of absorption with complications arising when the mesh product is resorbed too quickly. Rapid resorption does not support sufficient healing if structural reinforcement is diminished during the tissue repair period.

Therefore, some meshes contain chemicals to induce additional crosslinking in the graft. This slows down the degradation process, causing the mesh to retain its strength for a longer period of time [17]. However, crosslinking in the mesh reduces its biocompatibility; causing delayed cellular infiltration and neovascularization [17–19]. Ideally, a resorbable mesh should have a high ability to resist infections and retain its functional strength for a sufficient period of time to allow native cellular ingrowth tissue remodeling, maturation of collagen and gradual shift of mechanical load.

Phasix™ Mesh is a commercially available biosynthetic mesh. It is a slowly resorbable mesh prepared from poly-4-hydroxybutrate which has been studied for use as a biomaterial for different medical applications due its strength and flexibility, biocompatibility and desirable degradation times [20–22]. Phasix™ Mesh is comparable in performance to traditional polypropylene mesh when using standard measures of mechanical strength (suture pullout, tear and ball burst strength) [23, 24]. Preclinical implantation studies indicate that Phasix™ Mesh retains approximately 70% of its original strength at 12 weeks [23]. Absorption of the mesh material will be essentially complete in 12–18 months [24]. Given the long-term strength retention observed in preclinical studies, it is anticipated that Phasix™ Mesh may result in low recurrence and complication rates with minimal pain and discomfort when used for hernia repair.

### Rationale

From a general perspective, the current literature still is rather void of evidence-based guidelines regarding optimal choice of mesh. Simple, uncontaminated hernias are usually treated with synthetic mesh; biologic meshes are mostly used in potentially contaminated hernias, since post-operative mesh infection is anticipated.

Until now, the use of Phasix™ Mesh was studied primarily in patients up to VHWG Grade 2 [25].

Phasix™ Mesh has been studied prospectively until now in patients with a clean hernia site (CDC class I [26]) and up to VHWG Grade 2 [25, 27, 28]. A small retrospective study has also been conducted, showing positive results, but not elaborating on the exact contamination or size of the hernias [29]. Based on the data that will be gained from this clinical study, additional evidence may be provided with a view to optimal selection of hernia repair material in a population of higher risk. Since there is only limited knowledge on the treatment of VHWG Grade 3 patients, additional information is needed on safety and performance of the Phasix™ Mesh. Based on the combination of the features of the Phasix™ Mesh proven in previous clinical and non-clinical investigations, and based on evidence from the clinical study as described in this protocol, Phasix™ Mesh may become a preferred treatment option in VHWG Grade 3 patients.

## Methods

### Objectives

The objective of this study is to collect additional data on safety and performance of Phasix™ Mesh in subjects requiring VHWG Grade 3 midline incisional hernia repair. Among others, Surgical Site Occurrence (SSO), hernia recurrence, pain, infection, reoperation and adverse events will be collected for subjects with a VHWG Grade 3 hernia meeting the study inclusion and exclusion criteria.

### Design

The study has been designed as a post-market, prospective, single arm, multi-center, open-label study to collect data on performance and safety of Phasix™ Mesh in subjects with a VHWG Grade 3 midline hernia. This study will be conducted in 15 hospitals across Europe, which will each be allowed to include a maximum of 15 patients.

### Participants

Subjects with a VHWG Grade 3 incisional hernia scheduled for hernia repair are eligible for this study and will be asked for informed consent at the outpatient clinic. VHWG Grade 3 included, among others, previous wound infection after previous laparotomy (verified in the patient’s medical record), small bowel resection with anastomosis, take down of ileostomy with ileocolonic anastomosis, creation of a stoma, stoma present, jejunostomy, gastrectomy, and cholecystectomy. Patients with active infections, infected mesh, abscesses or active fistulas were not considered among patients with VHWG Grade 3. Patients solely at risk for an incidental enterotomy were not included in the population of which subjects could be drawn from.

#### Inclusion criteria

All subjects who meet the following criteria listed below can be enrolled in the study:Age 18 years or olderDiagnosis of an incisional midline herniaVHWG Grade 3 herniaSize of hernia > 10 cm^2^, as measured intraoperativelyElective retro-rectus hernia repairSigned informed consent

#### Exclusion criteria

All subjects who meet the following criteria must be excluded from study enrolment:

Regarding the subject:Body Mass Index (BMI) > 35 kg/m^2^PeritonitisUse or suspected future use of chemotherapeutic medication during any part of the studyKnown human immunodeficiency virus (HIV) infectionCirrhosis of the liver and/or ascitesPregnancy, plans to become pregnant during the study period or current breastfeedingAlcohol/substance abuse problem or a relapse within 12 months of the screening visitInvolvement in another interventional clinical study in the last 30 days prior to informed consent signatureLife expectancy of less than 2 years at the time of enrollmentKnown sensitivity to Phasix™ Mesh or component materials (subjects with known allergies to tetracycline hydrochloride or kanamycin sulfate)Any condition that, in the opinion of the investigator, would preclude the use of the study device or preclude the subject from completing the follow-up requirements

Regarding ventral hernia:More than 4 previous repairs of the hernia under observationThe hernia repair requires more than a single piece of meshIntact permanent mesh adjacent to the current hernia to be repaired

Regarding surgery:American Society of Anesthesiology class 4 or 5Surgical technique requires surgical bridge repairComplete removal of existing mesh from a prior hernia repair (in the same affected area) is not possibleThe hernia repair requires intraabdominal mesh placement

### Study procedures

#### Screening

Subjects with a diagnosis of incisional midline hernia requiring surgical repair to close the defect who are presenting at the study site will be considered potential subjects for inclusion in this clinical study and should be pre-screened for study eligibility. If inclusion criteria are potentially met and no exclusion criteria are anticipated to be present at the time of pre-screening, the Investigator will invite the subject to participate in the study.

#### Informed consent

Subjects will be asked to sign a written informed consent form. A copy of the informed consent will be provided to the subject.

#### Eligibility

Final eligibility will be determined intraoperatively. Subjects who fail to meet eligibility criteria should be considered screen failures and will be treated per hospital standard of care. Reason for screen failure will be documented. Screen failures are not considered drop-outs, and hospitals will continue to include patients until the required sample size has received surgery.

### Intervention

All subjects will undergo an open ventral repair of the hernia. All intraoperative inclusion and exclusion criteria will be verified.

Subjects will be administered perioperative antibiotics according to hospital protocol. Subjects will be prepared to undergo hernia repair with Phasix™ Mesh. The general instructions for the use of Phasix™ Mesh are supplied by the manufacturer.

#### Surgical technique

The surgical technique will require retro-rectus placement (onlay is allowed as an exception when retro-rectus placement cannot be achieved), using slowly resorbable sutures, with or without Component Separation Technique (CST). The peritoneum should remain posterior to the mesh upon completion of mesh placement. The mesh may be cut to shape or size desired for each specific application. The mesh is to be positioned so its edges extend beyond the margins of the defect by at least 5 cm. It is recommended that the mesh is fixated at approximately 5–6 cm intervals (6–12 absorbable sutures) around the periphery of the mesh. Defect closure must be confirmed. All skin incisions will be closed with staples/sutures and wounds will be dressed with sterile occlusive dressings.

### Outcome parameters

#### Primary outcome

Primary outcome will be Surgical Site Occurrence (SSO) up to and including, the 3-month follow-up assessment. SSOs will be assessed by physical examination at each study visit through 3 months. SSO is defined as hematoma, seroma, surgical site infection, wound dehiscence, skin necrosis and fistula, all of which require intervention.

#### Secondary outcome

Secondary outcomes will be:Surgical Site Occurrence (SSO) after the 3-month follow-up assessmentSurgical Site Infection (SSI) [26], is included in SSOs, but will also be analysed separatelyHernia Recurrence rate (via physical exam, if uncertain via ultrasonography, CT or MRI)Pain at every follow-up point, measured with the Visual Analogue Scale (VAS)Device related adverse event incidenceRate of reoperation due to the index hernia repairQuality of Life assessments (Carolinas Comfort Scale™ [30]^1^ and EuroQol-5D (EQ-5D) [31])Surgical procedure time as measured from incision to closure (skin to skin)Return to workLength of hospital stay (day of index surgery until day of discharge, LOS)

To measure these outcomes, the following data will be gathered at different points in time, and saved in an electronic case report form:

#### Pre-operative data

Demographic data (age, sex, race, ethnicity) and medical historyInformation regarding the inclusion and exclusion criteriaHeight and weight (calculated to a BMI)Length and width of herniaWound assessment○ signs of infection○ status and location of potential previous mesh○ signs of necrosisPain medication usagePain (measured with VAS), discomfort (measured with Carolinas Comfort Scale™) and quality of life (measured with EQ-5D)

#### Peri-operative data

Information regarding the inclusion and exclusion criteriaIntra-operative evaluation of wound and abdomenIntra-operative assessment and description of herniaIntra-operative assessment of complications, e.g. enterotomySurgical procedureMesh detailsFixation detailsWound closure

#### Post-operative data

The following data will be collected at fixed follow-up visits, namely at drain removal (if applicable, otherwise at discharge or at staple removal), 1 month, 3 months, 6 months, 12 months, 18 months and 24 months (Table 1):Wound assessment○ signs of infection○ status and location of potential previous mesh○ signs of necrosisHernia recurrence (diagnosed with physical exam, if uncertain via ultrasonography, or via CT/MRI)Adverse eventsDevice failure/malfunction/defectsPain (measured with VAS)Discomfort (measured with Carolinas Comfort Scale™)Quality of life (measured with EQ-5D)

**Table 1 Tab1:** Summary of procedures performed per visit

Study procedure	Screening and baseline	Index surgery	Drain removal/discharge	1, 3, 6 and 18 Month Visit	12 and 24 Month Visit	Early term
Describe study to potential subject	X					
Obtain informed consent	X					
Collect demographics and medical history	X					
Verify eligibility criteria	X	X				
Physical examination	X		X	X	X	X
Placement of device		X				
Pain Scale (VAS)	X		X	X	X	X
Carolinas Comfort Scale™	X			X	X	X
EQ-5D	X			X	X	X
Collect Adverse Events		X	X	X	X	X
Collect pain medications	X				X	

In addition, pain medication usage will be collected at 12 and 24 months follow-up.

#### Withdrawal/early termination

A subject is considered an Early Termination if discontinuation occurs after study treatment and before 24 months follow-up. The site will attempt to bring the subject back to the hospital to complete all Early Termination visit study procedures: Physical examination, Pain measured with VAS, Carolinas Comfort Scale™, EQ-5D and collect adverse events. Reason for subject discontinuation will be documented when possible.

### Sample size consideration

The expected rate of SSO at 3 months is 37% based on historical data (ranging from 21 to 53%) [32–35]. With 75 subjects, the accuracy of the estimated SSO will be ±11% (i.e. half of the width of the 95% confidence interval of the estimated rate of SSO is 11%). The study plans to enroll 85 subjects for follow-up. Anticipating on an attrition rate of about 10% after surgery, 75 subjects will be evaluable to assess the primary endpoint of Surgical Site Occurrence (SSO) at 3 months.

### Statistical analysis

There will be a modified intention-to-treat population (mITT), which consists of the subjects in whom Phasix™ Mesh has been implanted. The screen failures were not implanted, and therefore not used in the analysis. A per-protocol (PP) population may be created if there are subjects who have any major protocol deviations. However, all analyses will be primarily based on the mITT population.

Demographics and baseline characteristics will be summarized using the mITT population. Summary statistics for categorical variables will include frequency counts and percentages, and for continuous variables mean, standard deviation, minimum, median and maximum.

The primary endpoint is the SSO rate up to (including) 3 months (± 14 days) post device placement based on the mITT population. A 95% confidence interval will be reported for the SSO rate.

The SSO rate after 3 months, the hernia recurrence rates and surgical site infection rates until 1, 3, 6, 12, 18 and 24 months post device placement will be reported per visit along with their 95% confidence intervals based on the mITT population as secondary endpoints. Additionally, Kaplan-Meier analyses for the time from surgery to hernia recurrence and for the time from surgery to surgical site infection may be performed.

The secondary endpoints of VAS pain scale, Carolinas Comfort Scale™ and EQ-5D will be summarized based on the mITT population with mean, standard deviation, minimum, median and maximum presented by visit.

Device related adverse events will be tabulated by system organ class and preferred term. The number of subjects with a post procedure reoperation due to the index hernia repair will be presented by time intervals (until 1, 3, 6, 12, 18 and 24 months post device placement), surgical procedure duration of the index procedure (calculated as time of skin closure complete minus time of first incision) and length of hospital stay will be summarized descriptively. The time to return to work will be tabulated using summary statistics as well.

Safety parameters, such as adverse events, device deficiencies (mechanical failure, malfunction or defects), physical examination and pain medication, will be summarized using the mITT population.

Subgroup analyses will be performed by sex, sites (sites with few treated subjects can be combined) and other factors of interest.

No missing value imputation methods will be applied in any of the aforementioned analyses.

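### The 24-month recurrence rate is committed to as a per-visit rate with Kaplan-Meier only optional, so incomplete follow-up biases it, in a direction set by an unstated denominator

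*Protocol article*

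**What the plan says.** All of this is in the protocol article, Methods.

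- **Recurrence and surgical site infection (SSI).** Under Statistical analysis, the rates until 1, 3, 6, 12, 18 and 24 months "will be reported per visit along with their 95% confidence intervals based on the mITT population as secondary endpoints". The mITT population is everyone in whom the mesh was implanted.
- **Time-to-event analysis.** It is an optional extra: "Additionally, Kaplan-Meier analyses for the time from surgery to hernia recurrence and for the time from surgery to surgical site infection may be performed".
- **Missing data.** The same section rules out imputation in all of these analyses.
- **Return to work.** "The time to return to work will be tabulated using summary statistics as well". No rule is given for subjects who have not returned by last contact, or who were not working before surgery.
- **Attrition.** Under Sample size consideration: "Anticipating on an attrition rate of about 10% after surgery, 75 subjects will be evaluable to assess the primary endpoint". No attrition figure is given for 24 months.
- **Exit visit.** Under Withdrawal/early termination, the site tries to bring a leaving subject back for a physical examination and adverse event collection.

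**The concern.** A rate until month 24 is a cumulative risk. A subject who leaves at month 8 without recurrence contributes 8 months of information, and a proportion cannot use it. It must either count that subject as recurrence-free at 24 months or leave the subject out. The first choice pulls the rate down and the second pushes it up. A time-to-event estimate uses the 8 months as they are.

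This goes beyond a detail deferred to an analysis plan. The article itself names the committed estimate, makes the alternative optional and excludes imputation.

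The absolute rate matters here. The Background puts mesh absorption as essentially complete at 12 to 18 months, so recurrence by 24 months is the evidence on durability. With no control arm, readers will set the rate beside published rates, and an error in it does not cancel against a comparator.

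**Working it through.** **The plan's own figures.** The Sample size section gives an expected surgical site occurrence rate of 37%, 75 evaluable subjects and a half-width of ±11%.

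- 1.96 × √(0.37 × 0.63 / 75) = 0.109, which agrees.
- 75 / 0.9 = 83.3, so 84 subjects, against the 85 planned; 85 × 0.9 = 76.5. This is consistent with attrition of about 10%.

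These figures are not in dispute. They also mean that, on the plan's own assumption, cumulative loss by 24 months is at least about 10%.

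**Inputs for recurrence.**

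- True 24-month risk R: 23.8%, with 7.7% and 40% as the range. These are Background figures (primary closure, synthetic mesh, and the upper end for complex defects). They serve as illustration only and are not planning assumptions of the trial.
- Dropout by 24 months D: 10, 20 and 30%, assumed because the article gives none.
- Constant hazards, with dropout independent of recurrence.

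**Formulas.** Let a = −ln(1 − R) and b = −ln(1 − D).

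- Observed events as a share of all implanted: E = a/(a + b) × [1 − (1 − R)(1 − D)].
- Event-free completers: C = (1 − R)(1 − D).
- Version 1, all implanted as denominator: E.
- Version 2, events plus completers as denominator: E/(E + C).
- Kaplan-Meier targets R under these assumptions.

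**Worked case, R = 23.8%, D = 20%.** a = 0.2718, b = 0.2231, C = 0.762 × 0.8 = 0.6096. E = 0.2718/0.4950 × 0.3904 = 0.214. Version 2 = 0.2144/0.8240 = 0.260.

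| True risk | Dropout | All implanted | Events + completers |
|---|---|---|---|
| 7.7% | 10 / 20 / 30% | 7.3 / 6.9 / 6.5% | 8.1 / 8.6 / 9.1% |
| 23.8% | 10 / 20 / 30% | 22.6 / 21.4 / 20.2% | 24.8 / 26.0 / 27.4% |
| 40% | 10 / 20 / 30% | 38.1 / 36.2 / 34.2% | 41.4 / 43.0 / 44.8% |

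At 23.8% the error runs from −1.2 to −3.6 points in version 1 and from +1.0 to +3.6 points in version 2. For scale, the 95% half-width with 85 subjects is 1.96 × √(0.238 × 0.762 / 85) = 9.1 points.

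Timing of loss matters too. If the 10% left immediately after surgery, version 1 would give 0.9 × 23.8 = 21.4% and version 2 would be unbiased.

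**SSI.** Assume a 10% risk, all within the first 3 months, with dropout spread evenly in hazard over 24 months. Version 1 gives 9.9, 9.9 and 9.8%, so almost no bias. Version 2 gives 10.9, 12.0 and 13.4%.

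**Return to work.** Assume an exponential time with a median of 6 weeks among returners.

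- Loss to follow-up alone (10, 20, 30%) moves the observed mean only from 8.66 to 8.58, 8.50 and 8.41 weeks.
- If a fraction f never returns, the median over everyone is −6 × log2[1 − 0.5/(1 − f)]. For f = 10% this is 7.0 weeks and for f = 20% it is 8.5 weeks, against 6 weeks among returners.

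**Limit of Kaplan-Meier.** In a simulation with 20% dropout, a true risk of about 23.1% and a threefold higher dropout hazard in the higher-risk half, Kaplan-Meier gave 22.6%.

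**The case against.** The best defence has four parts.

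1. **The article fixes neither the denominator nor the interval method, and it foresees Kaplan-Meier.** An analysis plan that is not shown may settle both. This stands as far as the missing denominator goes, and "simple proportion" is an inference from the per-visit wording. It does not answer the point that the time-to-event estimate is explicitly secondary and optional.

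2. **The Early Termination visit catches events at exit.** It reduces missed recurrences up to that date. It does not supply the months after it.

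3. **The bias is modest.** At 10% dropout it is about one point, against a half-width of about nine. That is correct. More subjects would narrow the interval but not remove the bias.

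4. **These are descriptive secondary endpoints without a test.** Also correct, and it limits the weight of the point.

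Stronger readings are tempting, and the article does not support them:

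- **That loss to follow-up distorts all three outcomes.** Early SSI is almost unbiased over all implanted subjects, and for return to work the trouble lies with non-returners and subjects not employed.
- **That the error favours the mesh.** That holds only with all implanted subjects as denominator; with events plus completers it goes the other way.
- **That recurrences in subjects who later leave are dropped, so the cumulative rate could fall between visits.** This needs a denominator of visit attenders that discards known events. Rates defined as until each time, on the mITT population, do not suggest that.

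**Conclusion.** The point holds for 24-month recurrence. The committed estimate has no stated way to handle subjects whose follow-up ends early, and the method that does is optional. At an illustrative risk of 23.8% and 30% dropout, the same expected data could be reported as about 20% or about 27%, and neither is the target. At 10% dropout the gap is about one point either way.

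These sizes rest on assumed 24-month dropout, background recurrence figures, constant hazards and independent dropout. For SSI the change is mainly for consistency. For return to work the defect is one of definition: the summary describes only those who returned.

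The primary surgical site occurrence endpoint at 3 months, its precision and the sample size are untouched.

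**What to change.** - **Recurrence.** Make Kaplan-Meier, or cumulative incidence with death as a competing event, the planned estimate at 1, 3, 6, 12, 18 and 24 months, with 95% confidence intervals and numbers at risk.
- **SSI.** Use the same estimator for consistency.
- **Per-visit counts.** Keep them as descriptive and state their denominator.
- **Return to work.** Use Kaplan-Meier among subjects working before surgery, censoring those not returned at last contact.

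The cost is wording for recurrence and SSI, because the visits already supply the data. For return to work, work status before surgery must be on the case report form; the article's list of pre-operative data does not show it, though the full protocol may.

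The downside is small: Kaplan-Meier assumes non-informative censoring. Reasons for early termination are to be documented when possible, and reporting them beside the curve would let readers judge that assumption.
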